## Abstract

**Background:**

Sarcopenia refers to an age-related loss of skeletal muscle content, strength, and function, leading to a decrease in mobility. Obesity may exacerbate age-related complications such as sarcopenia through inflammatory pathways. In addition, intestinal dysbiosis has been proposed as an emerging contributor to sarcopenia due to the stimulation of the immune system and elevated barrier permeability of the intestine. Targeting microbiome with synbiotic and vitamin D supplementation may modulate the microbiome followed by the enhancement of sarcopenia indices. Thus, the present study aims to evaluate the effect of synbiotic supplementation with or without vitamin D on the intestinal microbiome and its relationship with strength, muscle function, and body composition in middle-aged overweight and obese women.

**Methods:**

This multi-factorial, double-blind, randomized controlled trial will be conducted on 88 participants in eight weeks. The participants will be allocated into four groups receiving vitamin D placebo (weekly) and synbiotic placebo (daily), vitamin D and synbiotic placebo, vitamin D placebo and symbiotic, and vitamin D and synbiotic. Intestinal microbiome assessment will be done by DNA isolation and real-time polymerase chain reaction (PCR). In addition, anthropometric indices, body composition, muscle strength, and physical performance will be evaluated by standard methods. All measurements will be made at the beginning and end of the study.

**Discussion:**

The previous studies showed that probiotics were involved in reducing inflammation, insulin sensitivity, modulation of atrophy markers such as atherogen-1, and decreasing reactive oxygen indices. In addition, vitamin D was found to improve the intestinal microbiome and facilitate muscle anabolism. The present protocol is novel as it aims to investigate the impact of the co-supplementation of synbiotic and vitamin D on the gut microbiome and sarcopenia indices.

**Trial registration:**

This trial has been registered in the Iranian Registry of Clinical Trials (IRCT20090822002365N25, date of registration: March 2021).

## Background

Sarcopenia has been described as the involuntary loss of skeletal muscle mass content and impairment of muscle function, which is accompanied by mobility decline, physical disability, decreased standing balance, high rate of hospitalization, and mortality [1, 2]. Sarcopenia, as a widespread condition, is prevalent in almost 15% of healthy elderly population up to 76% of hospitalized older adults [3]. Recent evidence has revealed the prevalence of sarcopenia to be approximately 21% among Iranian older adults [4]. This syndrome is accompanied by a wide burden and is rapidly influenced by increased age [5]. On the other hand, obesity may affect age-related complications, leading to sarcopenia by activating inflammatory pathways [6].

The pathogenesis of sarcopenia involves various aspects including replacement of fat instead of muscle fibers, muscle metabolism changes, neuromuscular junction degeneration, fibrosis increments, and oxidative stress [7]. Moreover, intestinal microbiome is an emerging contributor to health and diseases, and its interaction with different organs such as brain and liver has been investigated extensively. The possible communication between the gut microbiota and muscle has been posited recently as a “gut-muscle axis” [8]. Healthy gut microbiota can modulate physiological processes including the downregulation of inflammatory biomarkers and inflamm-aging, antioxidant capacity enhancement, insulin sensitivity improvement by the production of diet-derived polyphenols, B complex vitamins (B2, B9 and B12), ellagitannins, and short-chain fatty acids (SCFA), increased resistance to fatigue, enhanced mitochondrial biogenesis and energy production, stimulation of anabolism and cell production, gut barrier maintenance, and reduction of xenobiotic absorption [9–11].

Disruptions in the gut microbiome account for the pathogenesis of many complications. Furthermore, evidence has demonstrated that sarcopenia and physical weakness have been associated with intestinal dysbiosis due to the stimulation of the immune system, elevated barrier permeability of the intestine, and increased lipopolysaccharides levels [12]. Ultimately, this condition leads to muscle loss by creating a systemic inflammatory state. In addition, it has been shown in animal models that intestinal dysbiosis can disrupt neuromuscular transmission, leading to muscle protein catabolism [13]. Moreover, it should be noted that aging and obesity have similar consequences, and their synergistic influence on muscle function may exacerbate the health status [14]. Aging is correlated to gut microbiota alterations, and this shift is accompanied by bacterial diversity decline from Firmicutes, Bifidobacterium, and Bacteroides reduction to the expansion of opportunistic bacteria that have the potential to induce systemic inflammation [15]. On the other hand, diets with high sugar and fat contents can affect the pathways related to histidine, glutamate, SCFAs, macrophage activation, nuclear factor kappa B (NF-κB), and toll-like receptor (TLR) and change the intestinal microbiome balance, which is common in obesity, metabolic syndrome, and diabetes [16].

Targeting gut microbiota with nutritional supplements is a favorable approach for modulating the microbiome followed by the enhancement of muscle mass and function. For instance, dietary interventions with probiotics, prebiotics, and synbiotics facilitate weight loss/maintenance in obese individuals through microbiome improvements [17]. Probiotics also contribute to muscle physiology via increased access to amino acids, suppression of inflammatory cytokine production, and effects on bile acid metabolites [18]. In addition to synbiotics, vitamin D improves the intestinal microbiome function and homeostasis by downregulating inflammation, innate immunity enhancement, and intestinal barrier maintenance [19]. Some other mechanisms proposed for vitamin D include increasing the production of antimicrobial peptides (beta-defensin and cathelicidin) by macrophages, regulating the expression of tight junctions and adhesive binding proteins, and suppressing epithelial cell apoptosis that generally maintains the mucosal barrier function [20]. Vitamin D receptors (VDR) also play an important role in protecting probiotics against inflammation [21]. On the other hand, probiotics can have a synergistic effect with vitamin D by improving the expression of VDR [22, 23]. Overall, dietary interventions with synbiotic and vitamin D may play an essential role in modulating the intestinal microbiome. Following that, the healthy microbiome can be a mediator between nutrition and phenotypes associated with aging and obesity.

Based on what was mentioned above, it is vitally important to consider all the possible factors affecting the initiation of sarcopenia and investigate efficient interventions in line with these pathogeneses. Since synbiotics and vitamin D play different roles in improving the microbiome and no study has been done on the effects of these supplements on the gut-muscle axis, gut microbiome, and sarcopenia indices, the present study aims to evaluate the effect of synbiotic supplementation with or without vitamin D on the intestinal microbiome and their relationships with strength, muscle function, and body composition in middle-aged overweight and obese women.

## Methods

### Design

This study will be an eight-week, multi-factorial, double-blind, randomized controlled trial with four groups. The study population will consist of overweight and obese women over 40 years old before menopause who will be selected from the staff of Shiraz University of Medical Sciences referring to the cohort center of the University for follow-up. In order to encourage people to participate in the study, announcements will be prepared in their workplaces and an expert will be present in the cohort center to inform them about the aims and health benefits of the study. The participants will be recruited if they have insufficient vitamin D intake. The study will be conducted on eligible individuals using synbiotic (500 mg, once a day) and vitamin D_3_ (50,000 IU, once a week) supplementation for 8 weeks. The outcome measurements will be done at the beginning and at the end of the eighth week (Figs. 1 and 2). The protocol has been written in line with the Standard Protocol Items: Recommendations for Interventional Trials (SPIRIT) checklist.

**Fig. 1 Fig1:**
[figure not shown]
Flow diagram of the study protocol

**Fig. 2 Fig2:**
[figure not shown]
Timeline of the study (18 months have been expected for this trial)

### Objectives and hypotheses of the study

The primary objective is to determine the effect of co-supplementation with synbiotic and vitamin D_3_ on the intestinal microbiome. As the second objective, the study will evaluate the relationship between alterations in microbiome and muscle strength, muscle function, and body composition in middle-aged overweight and obese women. In addition, in order to control confounders, dietary intakes, physical activity, and exposure to the sun will be assessed at baseline and at the end of the study.

### Participants

The study will be performed on 88 overweight and obese women (body mass index (BMI) ≥ 25 kg/m^2^) aged 40–55 years, having insufficient vitamin D intake, not having taken vitamin D supplements orally or by injection during the past 2–3 months, not having reached menopause, not having taken synbiotic, probiotic, and prebiotic supplements during the past 2–3 months, not having the indications of chronic diseases such as diabetes, cardiovascular disease (CVD), uncontrolled blood pressure, and liver and kidney disorders, not taking supplements containing vitamins, minerals, and omega-3 or fish oil, not having taken antibiotics during the past 3 weeks, not following a special diet, not having used the medications that affect weight over the past 2 months, and not having used steroidal and non-steroidal anti-inflammatory drugs, anticonvulsants, anti-cholesterol drugs, antacids, diuretics, and laxatives over the past 2 months. The exclusion criteria will consist of being influenced by any acute diseases during the study, being less than 90% compliant with the intervention, and not being willing to continue the study.

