### Sample size

Due to the fact that the primary outcome of the research is gut microbiome assessment, the sample size was determined according to the study carried out by Most et al. [24], which evaluated gut microbiota composition in relation to the metabolic response to polyphenol supplementation in overweight individuals. Using the Standard Deviation (SD) of the logarithm of Firmicutes from that study (0.32), considering a difference equal to 1.25 SD (0.32 units of change in the logarithm of Firmicutes) between the two groups with the lowest and highest values of Firmicutes, and considering *α* = 0.05, *β* = 0.10, and a 10% dropout, a 22-subject sample size was estimated for each group. In total, 88 overweight and obese middle-aged women will be enrolled.

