#### Allocation concealment mechanism

In order to blind all the investigators and participants, an individual not involved in the trial will make a randomized list assignment for the participants in each group and will label all the identical containers (in appearance and color) based on their numbers. Therefore, the participants will be unaware of the type of the intervention they receive. The random sequence will be unpredictable, as well.

The 88 participants will be allocated into four groups at a 1:1:1:1 ratio, as follows:Receiving a vitamin D placebo soft gel containing paraffin (weekly) along with one capsule of synbiotic placebo containing 500 mg maltodextrin (daily) for 8 weeksReceiving a 50,000 IU vitamin D soft gel (weekly) along with one capsule of synbiotic placebo containing 500 mg maltodextrin (daily) for 8 weeksReceiving a vitamin D placebo soft gel containing paraffin (weekly) along with a 500 mg synbiotic capsule (daily) for 8 weeksReceiving a 50,000 IU vitamin D soft gel (weekly) along with a 500 mg synbiotic capsule (daily) for 8 weeks

The synbiotic capsules (GeriLact) will contain seven bacteria species (*Bifidobacterium longum* 3.5 × 10^9^ colony-forming units [CFU], *Lactobacillus casei* 3.5 × 10^9^ CFU, *Lactobacillus acidophilus* 10^9^ CFU, *Bifidobacterium breve* 10^10^ CFU, *Lactobacillus rhamnosus* 7.5 × 10^8^ CFU, *Lactobacillus bulgaricus* 10^8^ CFU, and *Streptococcus thermophilus* 10^8^ CFU per 500 mg), and 38.5 mg fructooligosaccharide. They will be manufactured by ZistTakhmir Co., Tehran, Iran. In addition, the placebo capsules with 500 mg maltodextrin content will be provided by the same appearance and color as the synbiotic supplement. Vitamin D soft gels and placebos containing paraffin will be produced by Zahravi, Iran. All the supplements will be placed in identical containers. The participants will be instructed to use the products. At the end of weeks 4 and 8, they will be asked to return the empty containers in order to count the number of remaining supplements for compliance assessment. The participants will also be contacted during the study to check their tolerance and to record the possible side effects of the supplements.

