#### Statistical analysis

Statistical analysis of the data will be performed using the SPSS 22.0 software (SPSS Inc., Chicago, IL). Initially, the Shapiro–Wilk test will be used for the evaluation of normality. The data will be reported as percentages for qualitative variables and mean ± SD for quantitative variables. Categorical variables will be compared using chi-square test. In addition, the baseline mean differences will be assessed using the analysis of variance (ANOVA). For assessing pairwise differences between the study groups, Tukey’s post-hoc test will be performed. Analysis of covariance (ANCOVA) will also be used to evaluate the intervention effects between the study groups with adjustment for baseline values. A logarithmic correction will be done for skewed data before analysis. Moreover, paired-sample *t*-test and Wilcoxon test will be used to compare the mean values of normally distributed and skewed data within groups after the intervention. To analyze the microbiome data, the fold expression change will be calculated. It should be noted that at 10% or higher dropouts, the intention to treat (ITT) analysis will be conducted. *P* < 0.05 will be considered statistically significant.

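### Randomised women can be excluded for illness or low compliance after allocation, intention-to-treat analysis is promised only at 10% or more dropout, and the 90% compliance rule is not defined for two products

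*Protocol article*

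**What the plan says.** Under Participants, the list of entry conditions is followed by this sentence: "The exclusion criteria will consist of being influenced by any acute diseases during the study, being less than 90% compliant with the intervention". It ends with a third item, unwillingness to go on with the study.

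Compliance is measured by counting what is left over. Under Allocation concealment mechanism, participants report at weeks 4 and 8, when "they will be asked to return the empty containers in order to count the number of remaining supplements for compliance assessment". All four groups take one soft gel a week and one capsule a day for 8 weeks, each either active or placebo. The article does not say whether the 90% applies to each product or to both together.

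Under Statistical analysis, the only statement on the analysis set is that "at 10% or higher dropouts, the intention to treat (ITT) analysis will be conducted". Under Sample size, the allowance for loss is given as "a 10% dropout, a 22-subject sample size was estimated for each group".

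**The concern.** An exclusion criterion normally acts before randomisation. These three cannot: each describes something that happens once a woman is already on her allocated products. Low compliance can follow from poor tolerance, and the article plans contacts during the study to check tolerance and record side effects. Acute illness may also depend on allocation, since the Background and Discussion credit both supplements with immune or anti-inflammatory effects. If such women are left out, those who remain in one group need not be comparable with those who remain in another. Adjusting the ANCOVA for baseline values does not restore the balance that randomisation gave.

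The ITT sentence does not settle this, because it makes the analysis set depend on the observed dropout rate. It also leaves open whether an excluded woman is a dropout, so it is unclear when the trigger is reached.

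**Working it through.** **Inputs from the article.** 88 women, 22 per group, four groups; 8 weekly gels and 56 daily capsules per woman, 64 units in all; compliance limit 90%; ITT trigger 10% dropout; α = 0.05, power 90%, 10% dropout allowance; planned difference 1.25 SD.

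**1. The plan's own sample size.** With a four-group ANOVA (noncentral F, noncentrality n × 1.25²/2, the two other groups at the midpoint), 90% power needs n = 20 per group. Then 20 × 1.10 = 22, as stated (20/0.90 = 22.2 would round up to 23). With all 22 per group analysed, power is 94%; with 20 it is 91%; with 19 it is 90%. This takes 1.25 SD at face value. The article also writes that difference as 0.32 log units, which is 1 SD when the SD is 0.32; at 1 SD, power with 22 per group is 78%. That inconsistency is a separate matter.

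**2. The ITT trigger.** 8/88 = 9.1% and 9/88 = 10.2%. Up to 8 women can be lost without any ITT analysis being promised.

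**3. The 90% rule under three readings.**

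| Reading | One gel missed, all capsules taken | Limit |
|---|---|---|
| Per product, gel | 7/8 = 87.5%, fails | no gel may be missed |
| Per product, capsule | 56/56, passes | 5 may be missed (51/56 = 91.1%; 50/56 = 89.3% fails) |
| Pooled units | 63/64 = 98.4%, passes | 6 may be missed (58/64 = 90.6%; 57/64 = 89.1% fails) |
| Average of the two percentages | (87.5 + 100)/2 = 93.75%, passes | with one gel missed, fails once 5 capsules are also missed (89.3%) |

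**4. How many women the choice of reading could affect.** The article gives no adherence data. Assume that each unit is missed independently with probability p. On the gels alone, P(fail) = 1 − (1 − p)⁸. Pooled, P(fail) = P(7 or more of 64 missed).

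| Assumed p | Fail on gels, per product | Of 88 | Left of 22 per group | Power at 1.25 SD | Fail, pooled |
|---|---|---|---|---|---|
| 1% | 7.7% | 7 | 20.3 | 92% | under 0.001% |
| 2% | 14.9% | 13 | 18.7 | 89% | 0.03% |
| 5% | 33.7% | 30 | 14.6 | 79% | 4.0% |

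The power column assumes that every failing woman is left out and nobody else is lost.

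**The case against.** A reader might infer that one missed gel already removes a woman. The article does not say so. It refers to compliance with the intervention, and in every group the intervention is a gel plus a capsule. On a pooled or averaged count one missed gel passes easily. A gel taken late also counts as taken, because compliance is a count of leftovers.

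A reader might also infer that the trial loses its planned 90% power. That is not shown. The miss rates above are assumptions, and the losses arise only on the per-product reading. If excluded women count as dropouts, the 2% and 5% scenarios pass the 10% trigger and ITT analysis applies. The 1% scenario, at 7.7%, stays below the trigger and keeps 92%. Nor does the article say that the 10% allowance leaves these removals out: unwillingness to continue is itself dropout, so taking a further 10% off the figures above has no support.

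Finally, the article does not say whether exclusion means stopping the supplements, ending follow-up or leaving the analysis, and a participant's own withdrawal cannot be overruled.

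These points stand, and they limit the finding. They do not remove it. Under 10% dropout no ITT analysis is promised, and the exclusions apparently apply. This is also not detail left to an analysis plan that is not shown, because the article states both the exclusions and the conditional rule.

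**Conclusion.** The concern holds in this form. The article excludes women on events after allocation and promises ITT analysis only when 9 or more of 88 are lost. With 1 to 8 women lost, the primary comparison apparently rests on a group selected by illness, compliance or willingness to continue. The direction and size of the resulting bias cannot be derived from the article. The bias does not depend on the per-product reading; it needs only that the excluded women differ between groups in ways related to outcome.

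The 90% rule is ambiguous for two products. The same woman, with one missed gel, is at 87.5%, 93.75% or 98.4% according to an unstated choice. The share of women failing could run from almost none to about a third over assumed miss rates of 1% to 5%. Loss of power is therefore a conditional, secondary point.

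**What to change.** Reconcile the Participants, Allocation concealment mechanism and Statistical analysis sections as follows.

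- State that acute illness and low compliance do not remove a woman from follow-up or from the primary analysis. This concerns data collection and analysis only, not whether supplements are continued.
- Measure every randomised woman at week 8 where she consents.
- Make analysis as allocated the primary analysis whatever the dropout rate, and delete the 10% condition.
- Treat withdrawal of consent as missing data, not as an exclusion criterion.
- Use the compliance count only to define a secondary per-protocol set, stated for each product, with a threshold that is workable on a count of 8.

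The cost is a change of wording and week-8 measurements for a few more women. Including less compliant women may dilute the estimated effect slightly; the secondary per-protocol set shows how far.

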### Ethics and trial registration

The study protocol has been registered in the Iranian Registry of Clinical Trials (IRCT20090822002365N25) and has been conformed to the Declaration of Helsinki Guidelines. It has also been approved by the Ethics Committee of Iran University of Medical Sciences, Tehran, Iran (IR.IUMS.REC.1399.1177). Written informed consent forms will be signed by all the participants. At the end of the study, vitamin D supplementation will be provided for the individuals receiving vitamin D placebo during the trial. Additionally, all the participants will have the opportunity to receive diet and food recommendations from the nutritionist.

### Sample size

Due to the fact that the primary outcome of the research is gut microbiome assessment, the sample size was determined according to the study carried out by Most et al. [24], which evaluated gut microbiota composition in relation to the metabolic response to polyphenol supplementation in overweight individuals. Using the Standard Deviation (SD) of the logarithm of Firmicutes from that study (0.32), considering a difference equal to 1.25 SD (0.32 units of change in the logarithm of Firmicutes) between the two groups with the lowest and highest values of Firmicutes, and considering *α* = 0.05, *β* = 0.10, and a 10% dropout, a 22-subject sample size was estimated for each group. In total, 88 overweight and obese middle-aged women will be enrolled.

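### The sample-size paragraph gives an SD of 0.32 and equates 1.25 SD with 0.32 log units; the three figures cannot all hold, so it is unclear which difference the 90% power refers to.

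*Protocol article*

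**What the plan says.** The Sample size section of the protocol article bases the calculation on the primary outcome, the gut microbiome, and on log Firmicutes in particular. Its inputs are:

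- The SD, taken from a cited polyphenol supplementation study: "Using the Standard Deviation (SD) of the logarithm of Firmicutes from that study (0.32".
- The target in SD units, with the same target in absolute units in brackets directly after it: "considering a difference equal to 1.25 SD (0.32 units of change in the logarithm of Firmicutes) between the two groups".
- The contrast: "between the two groups with the lowest and highest values of Firmicutes".
- Alpha 0.05 and beta 0.10, and then "a 10% dropout, a 22-subject sample size was estimated for each group".

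The total is 88. The allocation section confirms four equal groups: "The 88 participants will be allocated into four groups at a 1:1:1:1 ratio". The section does not name the test used for sizing.

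**The concern.** The bracket presents 0.32 log units as the translation of 1.25 SD, yet the SD just given is itself 0.32. On that SD the two versions of the target differ by a quarter (0.40 against 0.32). Rounding does not explain a gap of that size, and no other section corrects it.

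At stake is the meaning of the stated 90% power for the primary outcome. If the SD of 0.32 is right, a reader of a null result could believe that a 0.32 log-unit difference would have been missed only one time in ten, when the calculation behind 22 per group supports that only for about 0.40.

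**Working it through.** **Inputs** (Sample size section, with allocation from the Allocation concealment mechanism section): SD 0.32; difference 1.25 SD, also given as 0.32 log units; alpha 0.05; power 0.90; dropout 10%; four equal groups; 22 enrolled per group. Sidedness is not stated; two-sided tests or the overall F test are assumed.

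**Step 1: consistency of the three figures.**

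- 1.25 x 0.32 = 0.40 log units.
- 0.32 / 0.32 = 1.00 SD.
- For 1.25 SD to equal 0.32, the SD would have to be 0.32 / 1.25 = 0.256.

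**Step 2: reproduce the 22 per group.** The contrast between the lowest and highest groups is the usual maximum-minus-minimum input for a multi-group ANOVA. With two groups at the extremes, d SDs apart, and two at the grand mean, the noncentrality is lambda = n x d² / 2, with 3 and 4(n − 1) degrees of freedom.

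- d = 1.25, n = 19: lambda = 14.84, power 89.7%.
- d = 1.25, n = 20: lambda = 15.63, power 91.4%.

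So 20 completers are needed. Adding 10% gives 20 x 1.1 = 22, the protocol's figure. Dividing by 0.9 gives 22.2, rounded up to 23.

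**Step 3: other routes.**

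| Sizing test | d (SD) | n before dropout | n after dropout |
|---|---|---|---|
| Four-group ANOVA, two groups in the middle | 1.25 | 20 | 22–23 |
| Four-group ANOVA, two groups in the middle | 1.00 | 30 | 33–34 |
| Two-sample t, two-sided | 1.25 | 15 | 17 |
| Two-sample t, two-sided | 1.00 | 23 | 26 |
| Two-sample z, two-sided | 1.25 | 14 | 16 |
| Two-sample z, two-sided | 1.00 | 22 | 25 |
| Two-sample z, one-sided | 1.00 | 18 | 20 |

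Only the ANOVA at 1.25 SD reaches 22 with the stated dropout applied.

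**Step 4: power at each version of the target, if the SD is 0.32.**

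| Test | n per group | 0.40 (1.25 SD) | 0.32 (1.00 SD) |
|---|---|---|---|
| ANOVA, two groups in the middle | 20 | 91% | 74% |
| ANOVA, two groups in the middle | 22 | 94% | 78% |
| Unadjusted t, extreme pair | 20 | 97% | 87% |
| Unadjusted t, extreme pair | 22 | 98% | 90% |

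On the ANOVA basis with 20 completers, the difference detectable with 90% power is 1.22 SD, and 1.22 x 0.32 = 0.39 log units.

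**Step 5: if the SD is the slip.** With SD 0.256, a difference of 0.32 is 1.25 SD, and the 91% of Step 2 applies to 0.32 directly.

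**Step 6: sensitivity at 1.00 SD, n = 20.** Placing two groups in the middle gives the smallest noncentrality for a given range. If two groups sit at each extreme, as when only one of the two supplements acts, lambda = n x d² = 20 and the power is 97%.

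**The case against.** A reader might infer that the trial was designed for 0.40 log units and has roughly a one-in-four chance of missing the 0.32 it names. The documents do not support that as a settled fact, for four reasons.

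- **Any of the three figures may be the slip.** The SD comes from a cited study that is not at hand. With SD 0.256 there is no shortfall at 0.32.
- **The ANOVA basis is an inference.** No sizing test is named. A two-sided z calculation at 1.00 SD gives about 21.0, rounded up to 22, so 22 could also arise if the dropout allowance was never added. That contradicts the stated 10%, but it cannot be excluded. The preferred route also depends on multiplying by 1.1 and not dividing by 0.9.
- **The 74% belongs to the least favourable pattern of means.** With 20 per group, power at 1.00 SD runs from 74% through 87% (t test of the extreme pair) to 97% (two groups at each extreme).
- **The Statistical analysis section plans ANCOVA adjusted for baseline,** which can raise power. The gain depends on the baseline correlation, which is not given. As an illustration only, assumed correlations of 0.3, 0.5 and 0.6 would lift the 74% to 78%, 86% and 91%.

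It can also be said that a null result should be judged by its confidence interval and not by planned power, and that sample size, randomisation and analysis need not change.

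All of this limits the claim about power. None of it removes the contradiction, which is there whatever test was used.

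**Conclusion.** The inconsistency is certain: an SD of 0.32, a difference of 1.25 SD and a difference of 0.32 log units cannot all be true. The 22 per group best fits a four-group ANOVA at 1.25 SD, which accounts for every other stated input.

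The consequence for power is conditional. If the SD of 0.32 is right, the stated 90% belongs to about 0.40 log units, and on the sizing basis the power at 0.32 is about 74% to 78%, depending on whether 20 or 22 per group are evaluable. Other tests or patterns of means give higher values, and any gain from baseline adjustment cannot be computed from the document. If the SD is 0.256, the 90% at 0.32 stands and only the SD needs correcting. The document does not show which case applies.

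**What to change.** Keep the 88 women and correct the Sample size paragraph:

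1. Check the SD of log Firmicutes against the cited study.
2. Make the SD, the standardised difference and the log-unit difference agree. If SD 0.32 stands, restate the target as 1.25 SD = 0.40 log units and report the lower power at 0.32 under the sizing test (about 74% with 20 completers per group, if that test was the four-group ANOVA). If it does not stand, correct the SD.
3. Name the sizing test and the assumed arrangement of the four means, and say how the 10% dropout was applied.

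The cost is a source check and a sentence or two, with no extra participants. The downside is that the stated detectable difference may become less favourable. If 0.32 log units with SD 0.32 was the intended target and 90% power is to be held on the ANOVA basis, 30 completers per group would be needed, or 33–34 enrolled per group (132–136 in total). The protocol should therefore say openly which difference the 88 are meant to detect.
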